##### Aim #3

To compare changes in mammography screening Precaution Adoption Process Model decisional stage from baseline to 120 days post randomization between individuals in the **MI**^**2 **^and **C **study arms.

The PAPM outcome is a six-level ordinal measure and the predictor (treatment group) is dichotomous, so a 2 × 6 table will be generated. The Cochran-Armitagestatistic will be used to test the null hypothesis of no difference in the distribution of scores between these two groups versus a trend [70]. If serious imbalances are apparent from the descriptive statistics described above, we will use the cumulative logit model [67]. Predictor variables will include the intervention group and the unbalanced demographic characteristics to reduce the impact of these biases. Indicator variables identifying the community will also be included to control for this stratification variable as described by Agresti [67]. The results of this regression will be transformed into estimates of the proportion moving from one stage to the next, adjusted for the potential confounding variables. The fit of the model will be assessed using the Deviance statistic.

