In general, health behavior theories assume a certain level of knowledge about the health issue in question. After all, people need to know something to form perceptions and attitudes about the behaviors that lead to or prevent disease. Lack of awareness of the issue defines the PAPM's first stage. In the second stage, people become aware but are not yet at a point where they are actively considering the precautionary behavior. An individual in this stage lacks engagement due to inadequate personal relevance. Perceived susceptibility is presumed to be important at this stage. If, and when, people become engaged in the issue, they progress to a decision-making phase (Stage 3). Self-efficacy, barriers, and any prior experience with the screening test might be important in this decisional stage. Decision-making can result in a decision not to act (Stage 4) or a decision to act (Stage 5). However, deciding to act is not the final step in the process. It is at the decisional point that new barriers or low self-efficacy can again become apparent and need to be addressed directly. We propose addressing these issues through an application of the "implementation intentions" construct and have labeled this Action Implementation Intentions in the gap between decision and test completion. Our prior work [50] and other studies [8] have shown that even once a decision has been made and individuals are motivated to complete cancer screening, many individuals still fail to follow through with volitional features of testing procedures. This gap between decision and action is not unique to the PAPM [25,51].

The development of plans to overcome specific logistic or perceptual barriers can facilitate the translation of intent into action. For breast cancer, the decision to get screened may be separate from the decision of where to go to obtain screening services. Multiple steps are clearly involved in following through with test scheduling, completion, and follow-up. Our proposed project will explore and define these constructs as they apply to breast cancer prevention; the culturally sensitive intervention will test the model and its assumptions, and a 120-day post randomization follow-up survey will confirm participant progression through PAPM stages, determine changes in reported breast cancer screening barriers, and evaluate response to implementation intentions among minority women.

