### Aim #3

To compare changes in mammography screening Precaution Adoption Process Model decisional stage from baseline to 120 days post randomization between individuals in the **MI**^**2 **^and **C **study arms.

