#### Hypothesis

Individuals who receive the **MI**^**2 **^intervention will show significantly more movement in PAPM stage at 120 days post randomization than those receiving a general breast cancer prevention health education intervention (**C**).

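### Aim 3 ranks a decision against screening above being undecided and leaves out baseline stage, so refusals push the result towards benefit and the promised stage-to-stage movement cannot be estimated

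*Protocol article*

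**What the plan says.** Aim 3 compares changes in PAPM "decisional stage from baseline to 120 days post randomization between individuals in the" two study arms. Its hypothesis is that women receiving the MI2 "intervention will show significantly more movement in PAPM stage at 120 days post randomization"; it does not say which movements count as favourable.

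The Data Analysis section for Aim #3 fixes the method. It states "The PAPM outcome is a six-level ordinal measure", "so a 2 × 6 table will be generated", and the Cochran-Armitage statistic will "test the null hypothesis of no difference in the distribution of scores between these two groups versus a trend". If serious imbalances appear, a cumulative logit model replaces it. The predictors listed for that model are arm, the unbalanced demographic characteristics and community indicators. Its results are to be turned into "estimates of the proportion moving from one stage to the next".

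The Conceptual Model section numbers the stages. Women who become engaged are described thus: "they progress to a decision-making phase (Stage 3"). Then: "Decision-making can result in a decision not to act (Stage 4) or a decision to act (Stage 5"). The PAPM Stage section gives refusal its own response option, so stage 4 women can be identified. Project Instrumentation places the stage measure before randomisation, and the 120-day follow-up call repeats it. The follow-up section lists progression through the stages among the secondary outcomes.

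**The concern.** There are two separate problems.

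**Order.** A trend test and a cumulative logit model both read a higher category as further along. Under the article's numbering, an undecided woman who decides against screening rises from 3 to 4, although she has taken the branch away from screening. The analysis counts this partly as success. Any adverse shift of this kind would be masked, or would dilute a real effect in the other stages.

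**Baseline.** The aim and hypothesis concern movement from baseline, but the table and model describe stage at 120 days only. The section then promises movement proportions that such a model cannot supply.

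Aim 3 tests the behavioural model on which the intervention is built. What is at stake is the interpretation of that test, not the primary screening comparison.

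**Working it through.** **The plan's own figure.** No figure is given for Aim 3. The only design calculation is for Aim 1: 30% against 15%, two-sided α = 0.05, 80% power. With mean proportion 0.225:

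n = [1.960·√(2·0.225·0.775) + 0.8416·√(0.30·0.70 + 0.15·0.85)]² / 0.15² = (1.157 + 0.489)² / 0.0225 ≈ 120.5, so 121 per arm.

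The stated 121 reproduces (power 80.2%). It serves here only as a realistic arm size. A second size, 116, is 145 × 0.80, the completers at the planned 20% attrition.

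**Sign of the scoring error.** With equal arms, stage scores s_j, MI2 counts t_j, total counts n_j and overall N, the trend statistic is z = T/√V, where

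- T = Σ s_j (t_j − n_j/2)
- V = ¼ [Σ n_j s_j² − (Σ n_j s_j)²/N]

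Suppose the arms are identical except that k MI2 women are in stage 4 instead of stage 3. Then T = (k/2)(s₄ − s₃). With scores 1 to 6, T = +k/2, in favour of MI2 whatever the other counts. With stages 3 and 4 swapped, T = −k/2. With the two tied, T = 0.

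**Size, in an assumed table.** Control counts for stages 1 to 6 are 2/8/50/8/35/18 (sum 121). For k = 40 with scores 1 to 6: T = 20, Σ n_j s_j = 1006, Σ n_j s_j² = 4550, so V = ¼(4550 − 1006²/242) = 92.0 and z = 20/9.59 = +2.09.

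| k | Article's order | Stages 3 and 4 swapped |
|---|---|---|
| 10 | z = +0.50 | z = −0.56 |
| 20 | z = +1.01 | z = −1.09 |
| 30 | z = +1.54 (p = 0.12) | z = −1.61 (p = 0.11) |
| 40 | z = +2.09 (p = 0.037) | z = −2.10 (p = 0.036) |

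The cumulative logit model behaves the same way at k = 40: odds ratio 1.68 in favour of MI2 (p = 0.027) in the article's order, and 0.60 against it (p = 0.027) after the swap. Screened and decided-to-screen counts are equal in both arms throughout.

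**Size, in tables closer to the article's expectation.** The Conceptual Model section expects stages 2 to 4 together to be smaller than stage 5; the table above has 66 against 35. Four assumed control tables of 116 respect that expectation. In each, every stage 3 woman in MI2 is moved to stage 4 and scores are 1 to 6:

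| Control counts, stages 1–6 | Women moved | z |
|---|---|---|
| 1/3/8/3/84/17 | 8 | +0.62 |
| 1/5/15/5/73/17 | 15 | +1.00 |
| 1/8/25/6/59/17 | 25 | +1.45 |
| 2/8/30/8/51/17 | 30 | +1.66 (p = 0.10) |

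The sign is always wrong, but none is significant.

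**Baseline stage.** A change score on six levels runs from −5 to +5, which is 11 values. A table with six columns therefore holds stage at one time point. Such a table does not determine movement. If ten women are in stage 3 and ten in stage 5 at both visits, either nobody moved or all twenty changed places.

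Precision was checked by simulation (4,000 runs, 121 per arm). Assumed baseline proportions for stages 1 to 6 were 5/10/30/5/50/0%, and each woman moved up one stage with probability 0.30 in MI2 and 0.15 in control. The mean between-arm difference was 0.152 from 120-day stage alone and 0.151 from change. The standard deviations were 0.172 and 0.052, a ratio of about 3.3. The ratio is specific to this scenario, in which baseline and follow-up are closely related.

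**The case against.** The strongest case against has five parts.

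- **The scores are not written out, and a condensed article may leave them and the covariate list to an analysis plan.** This is partly fair. But the article does fix the scale, the table, the test and the model's predictors, and its numbering is the only order it offers. As written, stage 4 sits above stage 3.
- **A reader might infer that the planned test is likely to declare a false benefit.** The documents do not support that. It took about 40 women shifting, with no gain in intention or screening, in a table that runs against the article's own expectation.
- **A reader might infer that MI2 forces women into a decision and so raises refusals.** The intervention section says women who are unsure or unwilling are taken through information-seeking questions, and undecided remains a permitted staging answer. Nothing in the article predicts more refusals under MI2.
- **A reader might infer that Aim 3 cannot be answered at all.** That is too strong. Women are randomised individually and baseline stage is measured beforehand, so the expected difference in mean 120-day stage equals the expected difference in mean change. What is lost is precision and the transition proportions.
- **How low refusal should rank is a judgement.** This stands. With control counts 2/8/45/8/30/23 (116 per arm) and k = 20, ranking refusal below every other stage gives z = −2.45 (p = 0.014), a plain swap with stage 3 gives z = −1.06 (p = 0.29), and a tie gives 0. The first figure should not be presented as the correct answer.

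It is also true that the arm-by-stage table would show the stage 4 counts, so a large rise in refusals would be visible to a careful reader.

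**Conclusion.** The point holds in a limited form, and the Aim 3 section should be corrected. It contradicts the article's own model by placing refusal above indecision on a scale used for a trend. The direction of that error follows from the scores alone. Its size depends on how many women move from stage 3 to stage 4, which the article does not give, and every cell count used here is assumed. The realistic harm is a masked or diluted adverse shift; a falsely significant benefit would need an extreme one.

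The second half is an internal inconsistency: movement proportions are promised from a model that does not contain the starting stage. The 120-day comparison remains valid under randomisation, but it is less precise and does not measure the change named in the aim. Aim 3 is secondary, and the Aim 1 analysis is unaffected.

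**What to change.** Revise the Aim #3 analysis text before unblinded data are examined.

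1. Do not rank stage 4 above stage 3. Either define forward movement from baseline as yes/no, counting a move to stage 4 as non-progress and reporting stage 4 counts by arm separately, or pre-specify an order with stage 4 below stage 3 and a sensitivity analysis for its exact rank.
2. Make the main analysis a logistic model (forward movement) or cumulative logit model (120-day stage) with arm, baseline stage and the randomisation stratum or community as predictors.
3. Derive the movement proportions from the baseline-by-120-day cross-tabulation in each arm, or from the model that contains baseline stage.
4. State in the hypothesis which movements count as favourable.

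The cost is wording only. Both stage measurements are already planned, and no extra participants, visits or questions are needed.

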#### Sample Size and Sample Size Justification

This study will utilize Latina and AI/AN female participants from two distinct communities with approximately 121 randomized participants per community to test the main effects of the **MI**^**2 **^vs. **C **arms at 120 days post randomization. For this study, a total of 290 subjects will be randomized to either the **MI**^**2 **^or **C **treatment arms (to account for a possible 20% attrition rate from randomization to 120 day follow up). It is anticipated that 30% of those in the **MI**^**2 **^group will receive their breast cancer screening within the 120 day study period compared to 15% in the **C **group. A total of 242 subjects (121 per study arm) would have 80% power to detect the anticipated difference in screening rate between the **MI**^**2 **^and **C **groups at the α = 0.05 (two-sided) type I error rate (Table 5). Assuming up to a 20% attrition rate based on the research team's prior studies in rural Kansas, a total of 290 subjects will be randomized to either the **MI**^**2 **^or **C **treatment arms (145 per treatment). Additional screening rates were examined for study power (Table 5) to select an adequate sample size to detect clinically relevant differences. Numbers contained in Table 5 demonstrate that the sample will have at least 80% power to detect clinically relevant differences. Similar tables to Table 5 were also compared with varying sample sizes, with the final sample size selected being the choice that optimized both study power with the logistical constraints.

**Table 5 T5:** Power estimates (%) for a sample size of 121 subjects per group with α = 0.05 (two-sided)

		Breast Cancer Screening - Implementation Intentions	
		25%	30%
Breast Cancer Screening	10%	87	97
		
Controls	15%	Not Relevant	80

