#### Availability of Participants

We will recruit and randomize a total of 290 participants (145 randomized to the **MI**^**2 **^arm and 145 randomized to the **C **arm). Participants will be recruited from annually scheduled and well attended community events in and around the Mayetta and Garden City, KS communities. Garden City is the Finney County seat. Approximately 50% of the county population, and Garden City's population, is non-Hispanic White while 45% of the nearly 41,000 people living in Finney County are Latino (approximately 9,000 Hispanic/Latina females). Our American Indian recruitment in Northeast Kansas will include a five county region; Brown (pop. 10,009/52% female/9% AI/AN); Jackson (pop. 13,240/50% female/7% AI/AN); Doniphan (pop. 7,753/51% female/2% AI/AN); Jefferson (pop. 18,421/50% female/1% AI/AN); and Pottawatomie (pop. 19,695/50% female/1% AI/AN). The AI/AN female population in each county is: Brown = 470; Jackson = 452; Jefferson = 100; Potawatomie = 69; and Doniphan = 58.

Annual community events are common within both target communities. Amongst other events, Mayetta and surrounding areas are home to the Prairie Band Potawatomi Pow Wow (held in June) and Prairie Band Potawatomi Health Fair (September), Kickapoo Pow Wow (July), Sac and Fox Health Fair (September), and the Ioway Health Fair (October). Garden City and its surrounding communities is home to a Cinco de Mayo celebration (May), Community Mexican Fiesta (September), Tyson Health Fair (October), Binational Health Fair (October), and several community events sponsored by the six area churches. Using three CHWs per community, we anticipate being able to recruit approximately 150 women in each community. If, upon a midcourse evaluation, we determine that recruitment is behind schedule, we will supplement our recruitment efforts by partnering directly with health clinics in our target communities to recruit within clinic waiting rooms.

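### 290 women randomised with 20% attrition leave 232 evaluable, not the 242 required, so the stated 80% power is not reached at the stated attrition

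*Protocol article*

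**What the plan says.** All the key figures are in the protocol article, under Sample Size and Sample Size Justification.

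- **Planning rates:** "It is anticipated that 30% of those in the" intervention "group will receive their breast cancer screening within the 120 day study period compared to 15% in the" control group. The error rate is given as "α = 0.05 (two-sided) type I error rate (Table 5").
- **Requirement:** "A total of 242 subjects (121 per study arm) would have 80% power to detect the anticipated difference in screening rate". The Study 1 section repeats 121 per arm as the number required.
- **Allowance for loss:** "Assuming up to a 20% attrition rate based on the research team's prior studies in rural Kansas", 290 women are to be randomised, 145 per arm. The same section gives the same reason for the 290 a few lines earlier, calling the 20% a possible rate of loss between randomisation and the 120-day follow-up.
- **Number randomised, repeated:** Availability of Participants states "We will recruit and randomize a total of 290 participants", split 145 and 145.
- **Per community:** the section opens by describing two communities "with approximately 121 randomized participants per community to test the main effects".

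Table 5 gives power for 121 per group only. The document nowhere gives power at the number that would remain after 20% attrition.

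**The concern.** An allowance for a proportion lost has to leave the required number after the loss. The required number must therefore be divided by one minus the attrition rate. The 290 looks like the requirement multiplied by one plus the rate, which always gives too few. If so, the stated power and the stated attrition cannot both hold at 20%, and the section's claim of at least 80% power for clinically relevant differences fails in the scenario used to set the sample size.

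The per-community sentence is a second difficulty. It uses 121, the evaluable number per arm, as a number randomised per community. Taken literally, it means 242 randomised in total, which contradicts the 290 stated in the next sentence.

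**Working it through.** **Inputs (all from the sample size section unless noted).** p1 = 0.15, p2 = 0.30, two-sided α = 0.05 (z = 1.960), power 80% (z = 0.842), 1:1 allocation, 290 randomised, 20% attrition. The Aim #1 analysis section names a chi-square test on a 2 × 2 table.

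**1. Reproduce the plan's 121 per arm.** Pooled-variance formula without continuity correction, with mean rate p̄ = 0.225:

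n = [z(α/2)·√(2p̄(1 − p̄)) + z(β)·√(p1(1 − p1) + p2(1 − p2))]² / (p2 − p1)²

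- √(2 × 0.225 × 0.775) = √0.34875 = 0.5906
- √(0.1275 + 0.2100) = √0.3375 = 0.5809
- n = (1.960 × 0.5906 + 0.842 × 0.5809)² / 0.0225 ≈ 120.5, so 121 per arm, 242 in total

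This matches the plan. With a continuity correction the answer would be 134 per arm, so the plan used the uncorrected formula. Power at 121 per arm is 80.2% (15/30), 87.1% (10/25) and 97.7% (10/30), against 80, 87 and 97 in Table 5. So 121 is the evaluable number, and it carries almost no slack.

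**2. Check the inflation.**

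- Division: 242/0.80 = 302.5, so 303 (304 with equal arms, 152 each)
- Multiplication: 242 × 1.20 = 290.4; per arm 121 × 1.20 = 145.2

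Only the multiplication gives the plan's 290 and 145.

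**3. What 290 leaves.**

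- At 20% attrition: 290 × 0.80 = 232, or 116 per arm; 242 − 232 = 10 short
- Largest attrition that still leaves 242: 1 − 242/290 = 48/290 = 0.1655, about 16.5%

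**4. Power at 116 per arm, 15% versus 30%.**

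Power = Φ([0.15·√116 − 1.960 × 0.5906] / 0.5809) = Φ([1.616 − 1.157] / 0.5809) = Φ(0.789) = 78.5%

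| Method at 116 per arm (15/30) | Power |
|---|---|
| Pooled formula (reproduces the plan) | 78.5% |
| Unpooled formula | 79.4% |
| Exact power of the uncorrected chi-square test | 79.0% |
| With continuity correction | 73.5% |

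Every variant is below 80%. For the other two Table 5 cells, the pooled formula at 116 per arm gives 85.7% (10/25) and 97.2% (10/30).

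**5. Per community.** 290/2 = 145 randomised per community. Read literally, 121 randomised per community gives 242 randomised, and 242 × 0.80 = 193.6, about 97 per arm.

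**The case against.** Four points can be made for the plan.

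- **The 20% is a ceiling.** The text says up to 20%, and 80% power holds at any attrition up to about 16.5%. That is true, and it confines the shortfall to the top of the stated range. But an allowance for losses of up to 20% has to hold at 20%, and this one does not.
- **The loss is small and sits in one cell.** Power drops by 1.7 points (80.2% to 78.5%), which is minor beside the uncertainty in the planning rates. The section on the intervention impact estimate ends with 25% versus 10%, where power at 116 per arm is still 85.7%. This stands as a statement of size. It does not rescue the text, because the 80% claim is made for 30% versus 15%.
- **All 290 could be analysed.** The Aim #1 section counts women with unknown outcome as not screened, but only as a sensitivity analysis. With equal 20% loss in each arm, the rates become 0.8 × 15% = 12% and 0.8 × 30% = 24%; with 145 per arm, power is about 76%, which is lower still.
- **The per-community figure may be loose wording.** 242 evaluable over two communities is also 121 each, so the word randomised may be the only slip. That is plausible, and every other statement of the total says 290, so the 97-per-arm case is a literal reading and not a likely outcome. The sentence still conflicts with the one after it. Availability of Participants expects about 150 recruits per community, which agrees with 145 and not with 121.

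**Conclusion.** The concern holds. The 242 is correct for the stated rates, error level and power. The 290 does not follow from it at 20% attrition, because the inflation was done by multiplication. At the stated attrition the trial would have 232 evaluable women, 10 fewer than required, and power of 78.5% (79.0% exact) for 15% versus 30%. The stated 80% needs attrition of about 16.5% or less.

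The result assumes that the primary chi-square test uses women with a known outcome and that losses are equal in the two arms. The effect on the trial is modest: no design feature or test is affected, and the scenarios with a 10% control rate stay above 80%. As printed, however, the sample size statement for the primary outcome contradicts itself, and the per-community number is wrong as worded.

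**What to change.** Keep 290 and correct the text under Sample Size and Sample Size Justification:

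- State that 290 randomised leaves 242 evaluable, with 80% power for 15% versus 30%, if attrition is at most about 16.5%. At 20% attrition, 232 are evaluable (116 per arm) and power is about 78-79%.
- Table 5 is correctly labelled for 121 per group. Add the values at 116 per group, to the nearest point: 86% (10/25), 97% (10/30) and 78% (15/30, from 78.48%).
- Replace 121 randomised per community with 145.

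This costs wording only. No extra enrolment is needed, and the stated power becomes slightly less favourable. If the sponsor prefers to keep 80% power at 20% attrition, the alternative is to randomise 304 (152 per arm), which is 14 more women.

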#### Basis for intervention impact estimate

A study utilizing breast cancer survivors to serve as promotoras (similar to our community health worker paradigm proposed in this study) to promote breast cancer screening resulted in a 21% uptake in screening among 141 Latina women [71]. In a separate study with Native American women, a face-to-face patient navigator breast cancer education intervention resulted in a 11% uptake in screening mammography [72]. We expect a similar screening mammography uptake rates in our proposed study.

Screening uptake data from our current Healthy Living Kansas colorectal cancer implementation intentions intervention study are not yet available. However, other implementation intention-based studies have shown positive improvements in dietary fat intake [37], vitamin supplement intake [33], breast self-examination rates [34], vigorous physical activity rates [35], and functional ability after surgery [36]. Sheeran and Orbell [30] conducted a study to investigate the impact of an implementation intention intervention on cervical cancer screening rates - a behavior similar to the primary outcome of the proposed study, breast cancer screening. Sheeran and Orbell found the implementation intention intervention to increase cervical cancer screening attendance by 23% compared with a control group. Another recent study to assess the effect of implementation intentions on testicular self examination (TSE) in men found a 25% increase in self-reported TSE vs. a no intervention group. Both studies represent substantial behavioral changes resulting from implementation intentions-based interventions. Based on these studies, we would anticipate a similar increase in breast cancer screening in a general population. However, the participants who will be randomized into one of the proposed study arms represent traditionally underserved rural minority women whose access to mammography services may be hampered. Thus, we would expect for it to be more difficult to alter their breast cancer screening behavior. Nonetheless, based on the aforementioned assumptions, we anticipate a 25% increase in CRC screening rates for **MI**^**2 **^participants versus a 10% increase in breast cancer screening rates for **C **participants.

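### The sample size section and its stated basis give different expected screening rates, and the claim of at least 80% power for clinically relevant differences is not supported as written

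*Protocol article*

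**What the plan says.** Under Sample Size and Sample Size Justification, the protocol article sets the design rates: "It is anticipated that 30% of those in the" MI2 group will be screened within 120 days, "compared to 15% in the" C group. It then states: "A total of 242 subjects (121 per study arm) would have 80% power to detect the anticipated difference in screening rate between the" two groups, at the "α = 0.05 (two-sided) type I error rate". It randomizes 290 women (145 per arm) to allow for up to 20% attrition.

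Table 5 crosses control rates of 10% and 15% with MI2 rates of 25% and 30%, at 121 per group. It prints 87 (25% vs 10%), 97 (30% vs 10%) and 80 (30% vs 15%). The fourth cell, 25% vs 15%, is labelled Not Relevant. The text concludes: "Numbers contained in Table 5 demonstrate that the sample will have at least 80% power to detect clinically relevant differences".

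Basis for intervention impact estimate, the section meant to support these rates, ends differently: "we anticipate a 25% increase in CRC screening rates for" MI2 "participants versus a 10% increase in breast cancer screening rates for" C participants. Among the evidence it cites are a promotora study with 21% uptake and a study in Native American women where "a face-to-face patient navigator breast cancer education intervention resulted in a 11% uptake in screening mammography".

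**The concern.** Two things do not fit together.

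First, the section that should justify the design rates arrives at other rates, and names the wrong cancer for one of them; the trial's outcome is mammography. A reader cannot tell which pair the investigators expect.

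Second, the sentence on power is general, but only particular conditions support it. Table 5 has four cells. Three are at or above 80%, and the one without a figure turns out to be the only one below. The article defines no minimum clinically relevant difference and does not say why a 10-point gain falls outside the term, so the sentence holds only because that cell is set aside. It also rests on 121 evaluable women per arm, which the stated attrition does not leave.

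At stake is how the primary result can be read. The power statement is what a reader uses to judge which effects the trial could reasonably have missed.

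**Working it through.** **Inputs.** From the sample size section and Table 5: two-sided α = 0.05 (z = 1.960), 1:1 allocation, 121 evaluable per arm, 290 randomized, up to 20% attrition. From the Aim #1 analysis: χ² test on a 2 × 2 table.

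**Formula.** Pooled-variance normal approximation without continuity correction. With p̄ = (p1 + p2)/2,

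- SE0 = √[2 p̄(1 − p̄)/n]
- SE1 = √[(p1(1 − p1) + p2(1 − p2))/n]
- power = Φ[(|p1 − p2| − 1.960 × SE0)/SE1]

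**Step 1: reproduce the plan's figure (30% vs 15%, n = 121).** p̄ = 0.225, SE0 = 0.0537, 1.960 × SE0 = 0.1052, SE1 = 0.0528. Power = Φ[(0.15 − 0.1052)/0.0528] = Φ(0.848) = 80.2%. Solving the same formula for 80% power gives exactly 121 per arm.

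**Step 2: the whole of Table 5 at n = 121.**

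| MI2 vs C | Difference | Printed | Recomputed |
|---|---|---|---|
| 30% vs 15% | 15 points | 80 | 80.2% |
| 25% vs 10% | 15 points | 87 | 87.1% |
| 30% vs 10% | 20 points | 97 | 97.7% |
| 25% vs 15% | 10 points | Not Relevant | 49.4% |

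For the last row: p̄ = 0.20, SE0 = 0.0514, 1.960 × SE0 = 0.1008, SE1 = 0.0510, and Φ[(0.10 − 0.1008)/0.0510] = Φ(−0.015) = 49.4%. Other methods for this cell give 50.0% (unpooled variance), 49.9% (arcsine), 50.2% (exact power of the uncorrected χ² test), 43.0% (continuity-corrected) and 43.2% (Fisher). Reaching 80% for 25% vs 15% would take 250 evaluable per arm.

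**Step 3: attrition.** 290 × (1 − 0.20) = 232, or 116 per arm, not 242. (242 × 1.20 = 290.4, whereas 242/0.80 = 302.5; 290 leaves 242 only if attrition is 1 − 242/290 = 16.6%.) At n = 116:

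- 30% vs 15%: SE0 = 0.0548, SE1 = 0.0539, Φ(0.789) = 78.5%
- 25% vs 10%: 85.7%
- 25% vs 15%: 47.8%

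**Step 4: does 15 points always give 80%?** No; it depends on the control rate. At n = 121, 35% vs 20% gives p̄ = 0.275, SE0 = 0.0574, SE1 = 0.0566, Φ(0.662) = 74.6%. A corrected statement must therefore name the rates, not only the difference.

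**The case against.** The strongest reply is that no printed power is wrong. All three filled cells reproduce to within a point. The two rate pairs share the same 15-point difference, both appear in Table 5, and the trial is sized on the less favourable one. The text also says that further rates were examined for power. All of this stands.

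A reader might infer that the low-power cell was concealed. The documents do not support that: the cell is printed and openly labelled, and the sentence is limited to clinically relevant differences, so it agrees with its own table. What remains is that the label is unexplained.

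A reader might also infer that the trial has only 49% power for the effect its authors expect. That does not follow either. 25% vs 15% joins the MI2 figure of one section to the control figure of the other, and neither section anticipates it. The basis section does warn that behaviour will be harder to change in this population, but the assumed 15 points already lies below the 23% and 25% increases it cites from implementation-intention studies. Whether a 10-point gain matters is a judgement on which the article gives no reasoning in either direction.

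Finally, the basis section speaks of an increase, not a rate. Reading 25% and 10% as 120-day uptake is natural, because women enter not up to date and the figures match the margins of Table 5, but it is an interpretation.

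None of this reconciles the two sections, supplies a reason for the label, or restores the 121 per arm after 20% attrition.

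**Conclusion.** The point holds in a limited form. The article gives two unreconciled pairs of expected rates, one with a wrong cancer label. The inconsistency alone does not underpower the trial: at 121 evaluable per arm the pairs have 80.2% and 87.1% power.

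The general claim of at least 80% power for clinically relevant differences is unsupported as written, for two reasons. The only cell below 80% (about 49%) is excluded without a reason or a defined minimum relevant difference. And at the article's own 20% attrition the design pair has about 78%, not 80%. The second shortfall is small, under two points.

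These figures assume the uncorrected χ² test, which matches the printed values, equal arms, and attrition at the full 20%.

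**What to change.** 1. State one pair of expected 120-day mammography rates in both the sample size section and the basis section, and replace CRC with the mammography outcome.
2. Print about 49% in the 25%/15% cell of Table 5.
3. Limit the power sentence to its conditions, for example: 80% power for 30% vs 15% with 121 evaluable per arm (about 78% with 116 per arm after 20% attrition); about 49% for 25% vs 15%. Alternatively, keep the reference to clinically relevant differences, but state the minimum relevant difference and why 10 points falls short of it; the attrition condition is needed either way.

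The cost is wording only. The number randomized, the test and the conduct stay as they are; the stated power becomes somewhat less favourable.
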